### Key secondary outcome and moderation analysis

Assessments of abstinence in the 30 days prior to each of the 3-, 6- and 12-month follow-ups will also be analysed in the same way as the ITT analysis of the primary (2-week) endpoint – participants not assessed for any reason will be deemed to have relapsed. In a supplementary analysis of all available follow-up assessments (from 3 to 12 months), that assumes any missing follow-ups are missing completely at random, a logistic regression analysis, using the method of generalized estimating equations (GEE), will be used to compare the arms, and changes over time in the arms, adjusting, if need be, for sites. An additional supplementary, missing not at random (MNAR), analysis will use a Bayesian approach, and Markov chain Monte Carlo (MCMC) to jointly model abstinence and missingness. The model will include a random effect for each participant and minimally informative, normal prior distributions for parameters in the logistic models for abstinence and missingness. Parameter estimates and their associated 95% credible intervals, based on posterior distributions, will be reported. The MNAR approach will also be used to investigate the moderating effect of the baseline approach bias score. Additional exploratory analyses, also using the MNAR approach, will investigate adjusting the estimated difference between the arms for such covariates as age, gender, and SADQ score. Full details will be given in the statistical analysis plan (SAP) that will be documented prior to the analysis of the primary outcome.

### Other secondary outcomes

Other secondary outcomes that are binary will be analysed in the same way as the key secondary outcome measure, including supplementary analyses (as above). The moderating effect of baseline approach bias score on abstinence/relapse in the 2 weeks post discharge (i.e. the primary outcome) will be investigated by logistic regression models that include baseline scores as covariates in the model and tests of the significance of the two-way interaction of treatment arm with the covariate will be conducted. A similar approach will be used to test for a moderating effect of impulsivity, as measured by the BART.

Continuous-scale outcome measures, and ordinal scale outcomes that have five or more ordered categories, will be analysed using mixed models, and the restricted maximum likelihood (REML) method, with random effects for participants and assessments within participant, and fixed effects for treatment arm, time and baseline covariates. Diagnostic plots of residuals will be examined and, if required, analyses will be conducted using a variance-stabilising transformation such as the log transformation or the empirical logit transformation.

To determine the economic feasibility of CBM, in terms of savings to the treatment system (evidenced by fewer repeat inpatient withdrawal treatment episodes and episodes of acute health service use at the 12-month follow-up), we will compare net spending (cost of CBM intervention plus cost of further withdrawal/acute health service use for each participant) in the CBM group to net spending (cost of further withdrawal/acute health service use) in the control group. The statistical significance of the difference between the groups will be assessed with a *t* test and a variance-stabilising transformation, such as the logarithm, will likely be required.

For cue-evoked wanting, outcomes will be assessed with a mixed model (repeated measures) analysis assessing within-subjects variables of ‘time’ (pre-training/post-training), ‘picture-type’ (alcohol/non-alcohol), and ‘novelty’ (used in training/not used in training), with the between-subjects conditions of ‘group’ (CBM/Control). Particular attention will be paid to comparisons of time, picture-type, and group within each level of novelty. The number and proportion of participants who require cessation of one or more training sessions due to distress or fear of relapse, and who require permanent cessation of training for these reasons, will be reported as a measure of the safety of the CBM training. Statistical analyses will be conducted using the most appropriate procedures in GenStat, 19th Edition (VSN International, Hemel Hempstead, UK), SAS Version 9.4 (SAS Institute, Inc., Cary, NC, USA) and R (R Foundation for Statistical Computing, Vienna, Austria), or later versions of the software as they become available.

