## Background

Alcohol is one of the world’s most harmful drugs [1], responsible for 3.6% of deaths globally and 4.5% of the global burden of disease [2]. Alcohol consumption is a causal contributor to eight different cancers, numerous cardiovascular disorders (including hypertension, haemorrhagic stroke, and atrial fibrillation), pancreatitis, several liver diseases (notably cirrhosis and alcoholic hepatitis) and diabetes [3]. Excessive use can cause severe structural and functional neural abnormalities and result in significant cognitive dysfunction [4–6].

In Australia, alcohol is the most widely used drug, aside from caffeine. Despite recent evidence that people are drinking alcohol less frequently and more are choosing to abstain in recent years, many Australians continue to drink heavily and experience alcohol-related harm [7, 8]. Statistics indicate that more than one fifth of Australians meet lifetime *Diagnostic and Statistical Manual of Mental Disorders, Fourth Edition* (DSM-IV) criteria for an alcohol use disorder (AUD) [9]. Standard treatment for severe alcohol dependence in Australia often involves costly, intensive inpatient withdrawal treatment to manage acute withdrawal symptoms, followed by outpatient counselling and/or alcohol pharmacotherapy. Approximately 90% of patients relapse after withdrawal treatment, many within days of discharge, preventing successful engagement with post-withdrawal treatment and necessitating further episodes of inpatient withdrawal treatment [10]. Repeated readmission to withdrawal treatment, combined with this patient group's high rate of acute health service use, puts a high burden on the healthcare system. Novel interventions that reduce the proportion of patients who relapse have the potential to deliver cost savings to health and social welfare systems, and benefit alcohol-dependent individuals’ health and wellbeing, as well as their families.

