## Methods

### Aims

The primary objective is to determine the efficacy of CBM training, compared to sham training, in a population undergoing inpatient withdrawal treatment from alcohol, in terms of their abstinence rates at 2 weeks post-discharge.

The secondary objectives are:To determine the efficacy of CBM training compared with sham training, in a population undergoing inpatient withdrawal treatment for AUD, in terms of their abstinence rates at 3, 6, and 12 months post-discharge.To determine whether the efficacy of CBM compared to sham training is moderated by the strength of approach bias at baseline.To determine whether the efficacy of CBM is moderated by risk-taking impulsivity.To determine whether participants who undergo CBM training will demonstrate a reduction in self-reported cue-evoked desire (wanting) for alcohol compared to those who undergo sham training.To determine whether those who receive CBM training impose a lower burden on healthcare services in terms of reduced use of emergency healthcare services and readmission to alcohol and other drug (AOD) withdrawal treatment services in the year following discharge, relative to those who receive sham training. These data will be used to estimate the cost savings to the healthcare system that would be associated with introducing CBM as a routine component of inpatient withdrawal treatment.

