#### Service use

Use of AOD withdrawal treatment services, outpatient AOD counselling, AOD rehabilitation programs, general practitioner services, ambulance call-outs, emergency department visits, and hospital inpatient admissions are assessed with an interviewer-administered, modified version of the Lifetime Drug Use History Questionnaire (LDUH) [42]. At the baseline interview, these questions assess the year prior to the current inpatient withdrawal treatment admission. At each follow-up they assess the time since the previous follow-up (or since discharge in the case of the first follow-up since discharge, i.e. typically the 2-week follow-up), with data from the separate follow-ups then combined for each participant to form a composite assessment of service use over the whole 12-month follow-up period.

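### Net spending leaves out counselling, rehabilitation and GP use that the trial records, so it may overstate a healthcare-system saving and cannot tell a saving from a shift of cost

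*Protocol article*

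**What the plan says.** Under Other secondary outcomes, the article sets out the cost formula for each arm. The intervention arm is "net spending (cost of CBM intervention plus cost of further withdrawal/acute health service use for each participant) in the CBM group". The comparator is "net spending (cost of further withdrawal/acute health service use) in the control group". The purpose is economic feasibility "in terms of savings to the treatment system (evidenced by fewer repeat inpatient withdrawal treatment episodes and episodes of acute health service use", judged at 12 months. The Outcome measures section defines the cost outcome with the same two components, acute or emergency care and withdrawal readmission, and says a health economist will help with the costing.

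The Service use section records more than this: "Use of AOD withdrawal treatment services, outpatient AOD counselling, AOD rehabilitation programs, general practitioner services, ambulance call-outs, emergency department visits, and hospital inpatient admissions". The reports from the separate follow-ups are combined to "form a composite assessment of service use over the whole 12-month follow-up period".

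The Aims name emergency care and withdrawal readmission as the burden to be compared, and then say: "These data will be used to estimate the cost savings to the healthcare system that would be associated with introducing CBM as a routine component", meaning a component within the withdrawal units' usual care. The closing paragraph of the Discussion also hypothesises savings for the healthcare system as a whole.

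**The concern.** The Background says that relapse has two consequences: "preventing successful engagement with post-withdrawal treatment and necessitating further episodes of inpatient withdrawal treatment". The formula costs the second and leaves out the first. The Background's account of the pilot study gives the same reasoning for looking at the first 2 weeks after discharge: this is when engagement with ongoing treatment should begin, and rapid relapse often prevents it.

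On that reasoning, an effective intervention lowers readmission and raises use of post-withdrawal treatment. A sum that includes the first effect and omits the second leans towards showing a saving. At stake is whether a reported reduction means that the system spends less, or that spending has moved from withdrawal and acute units to counselling and rehabilitation services that were not counted. The result is meant to inform routine adoption, so the distinction matters, although this is a secondary outcome.

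**Working it through.** **What is recorded and what is costed**

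| Service | Recorded over 12 months | In net spending | Expected direction if CBM works, from the article |
|---|---|---|---|
| CBM delivery | not applicable | yes, CBM arm | added cost |
| Withdrawal readmission | yes | yes | falls (Background, Discussion) |
| Ambulance, emergency, inpatient | yes | yes (acute) | falls (Aims, Discussion) |
| Outpatient counselling | yes | no | rises: the Background names it as post-withdrawal treatment |
| Rehabilitation | yes | no | rises only if it is read as post-withdrawal treatment; not stated |
| GP | yes | no | not stated; could go either way |
| Alcohol pharmacotherapy | in part | no | rises: the Background names it as post-withdrawal treatment |

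Pharmacotherapy is captured only in part because the timeline follow-back covers the 2 weeks after discharge and then the 30 days before each of the 3-, 6- and 12-month follow-ups. That is at most 14 + 3 × 30 = 104 of 365 days, about 28%.

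**Can the size be computed?** No. The article gives no unit cost, expected use or expected saving, so there is no cost figure to reproduce. The one usable input is the conjectured abstinence difference in the Sample size section, 65% vs 45%, so d = 0.20. The sample size built on it reproduces (128 per arm, 256 in total, power 0.900), but that has no bearing on costs.

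**Illustration.** Everything except d is an assumption that is not in the article. Applying a 2-week difference to 12 months of service use is also an assumption.

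Let e be the extra probability that an abstinent patient takes up an omitted service, C the cost of one such episode, and g the change in all other omitted costs (for example GP) per additional abstinent patient.

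- Extra omitted episodes per 100 participants = 100 × d × e. For e = 0.10 this is 2; for e = 0.30, 6; for e = 0.50, 10.
- Overstatement of the saving per participant = d × (e × C + g). A negative value is an understatement.

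| e | C | g | d × (e × C + g) |
|---|---|---|---|
| 0.10 | 1,000 | 0 | 0.20 × 100 = 20 |
| 0.30 | 5,000 | 0 | 0.20 × 1,500 = 300 |
| 0.30 | 15,000 | 0 | 0.20 × 4,500 = 900 |
| 0.30 | 5,000 | −500 | 0.20 × 1,000 = 200 |
| 0.10 | 1,000 | −500 | 0.20 × (−400) = −80 |
| 0 | 5,000 | −500 | 0.20 × (−500) = −100 |

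The sign changes at e = −g / C. With g = −500, that is e = 0.50 at C = 1,000, e = 0.10 at C = 5,000 and e = 0.033 at C = 15,000. The direction therefore depends on quantities that the article does not supply. The trial will have recorded the service use that bears on them, and the net-spending formula does not use it.

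**The case against.** The strongest reply is that the narrow scope is openly and consistently declared. The Aims, the Outcome measures section and the economic paragraph all confine the outcome to acute care and withdrawal readmission. The Discussion also ties its expected health-system savings to those two items. A reader can see what is counted, and a partial costing perspective is a legitimate choice. This stands: nothing here is an internal contradiction. It does not make a system-wide conclusion valid, because a subtotal cannot show what happened to the rest of the spending.

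A second reply is that a broader costing could sit in the statistical analysis plan, which is not shown. That is possible. But the article itself fixes the formula and the claim to be drawn from it, so the mismatch is in what is stated.

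A reader might also infer that the trial expects counselling, rehabilitation and GP use all to rise, and hence that the saving is certainly overstated. The article does not support this. Only counselling, among the three recorded services, is named as post-withdrawal treatment. A rise in rehabilitation is an inference, and nothing is said about GP use, which could fall as drinking falls.

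Finally, a total of the collected services is not complete either, since pharmacotherapy is only partly captured. That is a fair limit on any fix.

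**Conclusion.** The point holds as a limit on inference. Net spending as defined omits three recorded service categories, at least one of which should rise on the trial's own rationale if CBM succeeds. It may therefore overstate a saving to the healthcare system, and it cannot distinguish a saving from a shift of cost.

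The lean towards a saving rests on one premise, the Background's link between early relapse and failed engagement in later treatment. It would be going too far to say that the comparison is biased in favour of CBM by a known amount, or even in a known direction. The range shown, from +900 to −100 per participant, comes from assumed uptake and unit costs; it shows sensitivity and is not an estimate. The comparison remains a sound basis for a statement about withdrawal and acute-care spending alone.

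**What to change.** Keep withdrawal plus acute cost as the declared outcome. Add a prespecified comparison of the total 12-month cost of all collected services: CBM, withdrawal readmission, ambulance, emergency, inpatient, rehabilitation, outpatient counselling and GP. Include GP for completeness, whichever way it moves. Report the declared outcome as a component of the total, so that any shift between services is visible.

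Base any statement about savings to the healthcare system on the total, and note beside it that alcohol pharmacotherapy is only partly captured. If the total is not added, word the conclusion as one about withdrawal and acute-care spending only, in the Aims and Discussion as well as in the results.

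The cost is small: unit costs for three more services, from the health economist already involved, and no new data collection. The downside is a more variable total and so a less precise comparison, which is a further reason to keep the narrower outcome alongside it.

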### Outcome measures

The primary outcome of interest to this study is the difference between treatment arms in proportion of participants reporting abstinence from alcohol 2 weeks after discharge, measured with the TLFB. Secondary outcomes of interest are abstinence at the subsequent follow-ups (measured with the TLFB), the difference between treatment arms in healthcare costs incurred due to acute/emergency healthcare treatment and readmission to AOD withdrawal treatment during the follow-up period (service use measured with the LDUH, with costs of treatment episodes to be estimated with the assistance of a health economist), and differences in cue-evoked desire for images of alcohol after the final session of CBM training. Secondary analysis will also examine the degree to which baseline approach bias towards alcohol moderates the effectiveness of CBM training on the primary outcome. Additional exploratory analyses are planned to investigate (i) moderating effects of pre-admission history of withdrawal treatment, severity of alcohol dependence and cravings, and impulsivity on the primary and secondary outcomes; (ii) whether alcohol cravings (as measured by the ACQ-SF-R) are affected by CBM; and (iii) whether CBM affects time to relapse.

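### The 12-month net-spending comparison is an unadjusted t test, although prior-year use of the same services is collected at baseline: a modest, nearly free gain in precision is left unused

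*Protocol article*

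**What the plan says.** The economic comparison has its own paragraph under Other secondary outcomes. The quantity compared in the CBM arm is "cost of CBM intervention plus cost of further withdrawal/acute health service use for each participant"; in the control arm it is the service cost alone. The test is fixed as follows: "The statistical significance of the difference between the groups will be assessed with a *t* test", and a log-type transformation is described as likely to be needed. No covariate, baseline value or site term is mentioned.

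Under Service use, the article lists withdrawal treatment and other alcohol and drug services, and then "ambulance call-outs, emergency department visits, and hospital inpatient admissions are assessed with an interviewer-administered, modified version of the Lifetime Drug Use History Questionnaire". Two sentences define the time windows. For baseline: "At the baseline interview, these questions assess the year prior to the current inpatient withdrawal treatment admission". For follow-up, the separate interviews are "combined for each participant to form a composite assessment of service use over the whole 12-month follow-up period". The trial will therefore hold the same service items for a year before and a year after the index admission.

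The paragraph just before the economic one sets the general rule for continuous outcomes: a mixed model whose fixed effects include baseline covariates as well as arm and time. The only planned use of prior service history that the article names is exploratory, under Outcome measures: "moderating effects of pre-admission history of withdrawal treatment, severity of alcohol dependence and cravings, and impulsivity on the primary and secondary outcomes". That is a question about moderation, not an adjustment of the cost comparison.

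**The concern.** Lower use of emergency services and fewer withdrawal readmissions in the year after discharge, with the resulting cost saving, is a stated secondary objective (Aims). The sample was sized for 2-week abstinence, not for cost, and the article expects about 70% retention at 12 months. Precision for this comparison will be limited.

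Past service use is a natural predictor of later service use. An unadjusted test leaves all of that predictable between-person variation in the error term. Randomisation is stratified by site alone (Allocation), so prior use is balanced only in expectation. If one arm happens to contain people with more prior use, the unadjusted difference carries part of that imbalance into the estimated saving. The data needed to remove it are already being collected.

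**Working it through.** **The plan's own figure.** The article gives no power or detectable difference for cost. Its only power statement is for the primary outcome (Sample size): 65% against 45%, two-sided alpha 0.05, pooled variance, 90% power. Per arm, n = [1.960·√(2·0.55·0.45) + 1.282·√(0.65·0.35 + 0.45·0.55)]² / 0.20² = (1.379 + 0.883)² / 0.04 ≈ 128, or 256 in total. This reproduces the stated figure but says nothing about cost.

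**Inputs for the cost comparison.**
- Randomised: 150 per arm (Sample size).
- With 12-month data: about 0.70 × 150 = 105 per arm (retention figure in the Discussion).
- Correlation ρ between prior-year and follow-up cost on the analysis scale: not in the article. Assumed range 0.2 to 0.5.

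**Gain from adjustment.** Adjusting for the baseline value multiplies the error variance by 1 − ρ². If the t test has 80% power, its noncentrality is 1.960 + 0.842 = 2.802. Adjusted power is Φ(2.802/√(1 − ρ²) − 1.960). The difference detectable with 80% power at 105 per arm is 2.802·√(2(1 − ρ²)/105) SD, which is 0.387 SD for the t test (ρ = 0).

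| ρ | Variance factor | Interval narrower by | Power (from 80%) | Detectable difference | Equivalent gain in n |
|---|---|---|---|---|---|
| 0.2 | 0.96 | 2.0% | 82% | 0.379 SD | 4% |
| 0.3 | 0.91 | 4.6% | 84% | 0.369 SD | 10% |
| 0.4 | 0.84 | 8.3% | 86% | 0.354 SD | 19% |
| 0.5 | 0.75 | 13.4% | 90% | 0.335 SD | 33% |

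**Which ρ is plausible.** The scale matters. As an illustration on assumed inputs, take costs that are zero for 30% to 50% of people and lognormal otherwise (log-SD 1.0 to 1.5), with an underlying correlation of 0.5 between the two years. The correlation of the untransformed costs is then only about 0.2 to 0.4, and 80% power becomes about 82% to 86%. With an underlying correlation of 0.3, the untransformed correlation is about 0.1 to 0.2 and power is 80% to 82%.

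**Chance imbalance.** At 105 per arm, the difference in mean prior-year cost has a standard error of √(2/105) = 0.138 SD. An imbalance of one standard error shifts the unadjusted result by ρ standard errors: at ρ = 0.5, by 0.5 × 0.138 = 0.07 SD.

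A simulation of 8,000 trials per setting (105 per arm, normal data on the analysis scale, no true effect) gave the t test an overall false-positive rate of 4.9% to 5.5%. In trials where prior use differed by more than 1.5 standard errors, which happens in about 13% of trials (2·[1 − Φ(1.5)] = 0.134), the rate was about 9% at ρ = 0.3 and 14% at ρ = 0.5. With adjustment it was about 6% in both.

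**The case against.** **The planned test is valid.** Under randomisation its false-positive rate is 5% on average and its standard error already allows for chance imbalance. A reader might infer from the missing covariate that the cost result will be biased. The article does not support that. The exposure is conditional on an unlucky allocation, and a typical imbalance moves the estimate by half a standard error or less over the range of ρ considered. This objection stands, and it confines the point to efficiency and robustness.

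**The plan does address variable costs.** It foresees a variance-stabilising transformation, so the test is not a naive comparison of raw costs. That also stands. However, a transformation deals with skewness; it does not use the information in prior-year use.

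**The gain may be negligible.** The article gives no correlation, and at 0.2 to 0.3 the gain is 2 to 4 power points. It is also tempting to read the Background as showing that a minority of repeat users drives cost, which would make imbalance more dangerous. The Background speaks of high acute-service use and repeated readmission in the patient group as a whole, so that inference has no support in the text.

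**The covariate is imperfect.** Baseline is one 12-month recall, while follow-up adds up shorter recall periods. Some baseline service-use forms are completed on training day 2 or 3, after randomisation (Procedure), and some secondary measures may be dropped because of fatigue, distress or lack of time (Discussion). These are real but small limits. The late forms still ask about the year before admission, and missing forms can be handled by a simple rule.

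**The unseen SAP may add an adjusted analysis.** It may. But the article fixes the unadjusted test rather than leaving the choice open, and an SAP that follows it would carry that test forward.

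**Conclusion.** The point holds as a modest improvement to a secondary analysis. The net-spending comparison is fixed as an unadjusted two-group t test, a baseline measure of the same services over a window of equal length is collected, and the article gives no reason for not using it.

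The cost is lost precision and avoidable exposure to chance imbalance, not invalidity. Its size rests wholly on an assumed correlation. From 80% power, the gain is about 2 points at 0.2, 4 at 0.3, 6 at 0.4 and 10 at 0.5, with the lower end more plausible if untransformed costs with many zeros are analysed. These figures also assume approximate normality of the estimate and about 105 per arm with 12-month data. The primary outcome is unaffected.

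**What to change.** Before the outcome is analysed, replace the t test with a regression of 12-month net spending on treatment arm, site and prior-year cost. Compute prior-year cost from the baseline questionnaire with the same service items and unit prices as at follow-up.

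Put outcome and covariate on one pre-specified scale. Either keep the planned transformation for the significance test, or analyse mean cost directly with a robust or bootstrap confidence interval. The second option matches the objective more closely, because savings are judged on mean cost.

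Keep the unadjusted comparison as a supportive result. Where the baseline service-use value is missing, fill it with the overall mean, blind to arm, and add a missing-value indicator, so that no participant with follow-up cost is lost from the model.

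The cost is a few sentences of analysis text and the pricing of items already collected; no new data or participants are needed. The SAP should acknowledge that some baseline forms are completed after randomisation, although they refer to the year before admission.

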### Sample size

Our recent pilot study indicated a difference in abstinence rates of 22% (i.e. 69% vs 47%) between the CBM and sham training groups. Using a smaller conjectured difference of 20% (e.g. 65% vs 45%) a two-sample, binomial test (two-sided α = 0.05) that utilises a pooled estimate of the variance, has 90% power to detect the conjectured difference when a total of 256 participants is randomised (i.e. 128 in each treatment arm). With an allowance for up to 15% drop out in the 2 weeks after discharge, based on an observed retention rate of 86% at 2 weeks in the pilot study, the target sample size was set at 300 (i.e. 150 randomised to each treatment arm). Recruitment is expected to take 22 months, given the throughput in the withdrawal treatment units, and the total study duration is likely to be 36 months.

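### The t test of net spending, with a logarithm as its likely transformation, does not compare mean costs and meets zero costs in the control arm only, so its result would depend on how zeros are handled

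*Protocol article*

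**What the plan says.** The fifth secondary objective (Protocol article, Aims) asks whether CBM reduces use of emergency care and readmission to withdrawal treatment over the following year, and continues: "These data will be used to estimate the cost savings to the healthcare system". Outcome measures lists as a secondary outcome "the difference between treatment arms in healthcare costs incurred due to acute/emergency healthcare treatment and readmission to AOD withdrawal treatment during the follow-up period".

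Other secondary outcomes defines the quantity compared. In the CBM arm it is "cost of CBM intervention plus cost of further withdrawal/acute health service use for each participant". In the control arm it is "net spending (cost of further withdrawal/acute health service use) in the control group". The arms are then compared by a *t* test, with the expectation that "a variance-stabilising transformation, such as the logarithm, will likely be required".

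The article does not say how a zero cost would be transformed. It names no back-transformation and no comparison of mean costs on the original scale.

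**The concern.** Two features of this analysis conflict with its purpose.

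- **Zeros fall in one arm only.** Only withdrawal and acute services count towards net spending, so a control participant who used neither costs exactly zero. A CBM participant with the same history costs the price of the training. The log exists for the second and not for the first. Since CBM is expected to save money through fewer episodes, participants with no episodes carry much of the effect of interest.
- **The scale is wrong for savings.** What a health system saves is the number of patients times the difference in arithmetic mean cost. A t test on logs compares geometric means, and the two differences can have opposite signs when the spread of costs differs between arms.

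At stake is the significance statement for a stated secondary objective. The Discussion looks to cost savings as part of the case for adopting CBM, so a result in the wrong direction could mislead health services.

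**Working it through.** The plan gives no numerical figure for the cost analysis, so there is none to reproduce.

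**Input from the article.** 150 per arm (Sample size: "the target sample size was set at 300 (i.e. 150 randomised to each treatment arm").

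**Assumptions, not in the article.** Costs among service users are log-normal with median AUD 5000 and log-SD 1.2. The CBM cost is c = AUD 100 for everyone in that arm. The share of participants with no counted use is 40%, varied from 5% to 50%. The test is a two-sided 5% Welch t test. The ways of treating zeros (adding a constant k, or dropping them) are also assumed.

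**Step 1: why the constant matters.** With equal service use, the log-scale gap among participants without service use is log(c+k) − log(k). Weighted by 40%, this gives:
- k = 1: 0.4 × log(101) = 1.85
- k = 100: 0.4 × log(2) = 0.28
- k = 1000: 0.4 × log(1.1) = 0.04

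The simulated total gaps are 1.87, 0.30 and 0.05, so the same AUD 100 produces most of the gap, and k sets its size.

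**Step 2: equal service use.** CBM is truly dearer by AUD 100, against a control mean of 0.6 × 5000 × exp(0.72) = AUD 6163.

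| Share with zero cost | log(cost+1): dearer | log(cost+100): dearer | log(cost+1000): dearer | Control zeros dropped: cheaper |
|---|---|---|---|---|
| 10% | 46% | 8% | 4% | 56% |
| 20% | 83% | 11% | 4% | 98% |
| 30% | 97% | 18% | 5% | 100% |
| 40% | nearly 100% | about 25% | about 6% | 100% |
| 50% | 100% | 35% | 7% | 100% |

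At 40% zeros, a square root finds CBM dearer in about 10%. The raw-scale test is significant in either direction in under 5% in total. A finding of dearer has the right sign here, but it reflects the fixed training cost and not service use. A finding of cheaper is simply wrong.

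**Step 3: a true saving.** Let CBM reduce the share of service users from 60% to 50%. Mean net spending is AUD 6163 in controls and 0.5 × 5000 × exp(0.72) + 100 = AUD 5236 under CBM, a saving of AUD 927.

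| Test | CBM significantly dearer | CBM significantly cheaper |
|---|---|---|
| log(cost+1) | 97% | 0% |
| log(cost+10) | 47% | 0% |
| log(cost+100) | 2% | 3% |
| log(cost+1000) | 0.2% | 16% |
| raw cost | 0.3% | 9% |

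The direction of the significant results changes with k.

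**Step 4: no zeros at all.** Let the log-SD be 1.5 in controls and 0.9 under CBM, with the log median 0.4 higher under CBM. The means are 5000 × exp(1.125) = AUD 15,401 and 5000 × exp(0.4 + 0.405) + 100 = AUD 11,283, so CBM saves AUD 4118. The log t test still finds CBM dearer in 84% of trials.

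**Step 5: retention.** With the roughly 70% retention at 12 months anticipated in the Discussion (105 per arm) and 40% zeros, log(cost+1) finds CBM dearer in 98% under equal use and in 89% under the AUD 927 saving. Dropping control zeros finds it cheaper in 100% under equal use.

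**The case against.** The strongest reply is that the article commits to no log test. It fixes a t test, says a transformation will likely be needed, and offers the logarithm as an example. The exact transformation and the rule for zeros are usual content for the analysis plan, which the article promises. This stands: neither log(cost+1) nor the dropping of zeros is in the document, and milder choices do much less harm. It does not remove the point, because the logarithm is the one transformation named for this analysis, and other nonlinear transformations do not compare mean costs either. An analysis plan that followed the article would inherit the mismatch.

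The inputs are also assumed. The Background reports about 90% relapse and heavy use of acute services, so 40% without any counted use may be high. With 5% zeros and a CBM cost of AUD 20, log(cost+1) finds CBM dearer in only about 9% of trials.

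A reader might infer that the economic objective as a whole cannot be answered. The text does not support that. The transformation is attached only to the significance test, and nothing ties the estimate of savings itself to the log scale.

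**Conclusion.** The point holds as a mismatch between a stated method and its stated aim. The asymmetric zeros follow from the article's own definitions as soon as some control participants use no counted service, and the geometric-mean problem needs no zeros. Both concern the significance test of one secondary objective. The primary outcome and the abstinence analyses are untouched.

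A wrong direction is possible, not certain. Under the assumed 40% zeros and AUD 100 training cost with equal use, results run from about 6% dearer to nearly 100% dearer, or 100% cheaper, depending on the handling of zeros alone. The extreme figures describe particular zero rules and should not be read as what this trial will produce. It should be corrected before the cost data are analysed.

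**What to change.** Make the main cost analysis the difference between arms in arithmetic mean net cost per participant, in AUD, with a bootstrap or Welch 95% confidence interval. A generalised linear model for costs is an alternative if the mean difference is recovered in AUD. Keep any transformed test as supportive only, with its treatment of zeros stated in advance.

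Optionally, adjust for service use in the year before admission. The baseline interview collects that use but not its cost, so it would have to be costed first.

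The change costs some wording in the analysis plan and a little analysis work, and needs no new data. The drawback is precision. With costs this skewed, the raw-scale test detects the AUD 927 saving in only about 9% of trials under the assumptions above, so the interval should be reported and not just a p-value.
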